## Abstract

**Background:**

Individuals with a personal or family history of cancer, can opt for genetic counseling and DNA-testing. Approximately 25% of these individuals experience clinically relevant levels of psychosocial distress, depression and/or anxiety after counseling. These problems are frequently left undetected by genetic counselors. The aim of this study is to evaluate the efficacy of a cancer genetics-specific screening questionnaire for psychosocial problems, the ‘Psychosocial Aspects of Hereditary Cancer (PAHC) questionnaire’ together with the Distress Thermometer, in: (1) facilitating personalized counselor-counselee communication; (2) increasing counselors’ awareness of their counselees’ psychosocial problems; and (3) facilitating the management of psychosocial problems during and after genetic counseling.

**Methods:**

This multicenter, randomized controlled trial will include 264 individuals undergoing cancer genetic counseling in two family cancer clinics in the Netherlands. Participants will be randomized to either: (1) an intervention group that completes the PAHC questionnaire, the results of which are made available to the genetic counselor prior to the counseling session; or (2) a control group that completes the PAHC questionnaire, but without feedback being given to the genetic counselor. The genetic counseling sessions will be audiotaped for content analysis. Additionally, study participants will be asked to complete questionnaires at baseline, three weeks after the initial counseling session, and four months after a telephone follow-up counseling session. The genetic counselors will be asked to complete questionnaires at the start of and at completion of the study, as well as a checklist directly after each counseling session. The questionnaires/checklists of the study include items on communication during genetic counseling, counselor awareness of their clients’ psychosocial problems, the (perceived) need for professional psychosocial support, cancer worries, general distress, specific psychosocial problems, satisfaction with care received, and experience using the PAHC questionnaire.

**Discussion:**

This study will provide empirical evidence regarding the efficacy of a relatively brief psychosocial screening questionnaire in terms of facilitating personalized communication, increasing counselors’ awareness, and optimizing management of psychosocial problems in the cancer genetic counseling setting.

**Trial registration:**

This study is registered at the Netherlands Trial Register (NTR3205) and ClinicalTrials.gov (NCT01562431).

## Background

Genetic counseling is offered to individuals who are at high risk of carrying a cancer gene mutation and who are at high risk of developing hereditary cancer. Factors related to *hereditary* cancer are: a cancer diagnosis at a young age, multiple relatives with a similar cancer diagnosis or a specific combination of cancers and a proven gene mutation in the family
[1]. Reviews of previous studies indicate that, on average, genetic counseling does not have adverse psychological effects (i.e., depression, anxiety, distress). However, approximately 25% of high risk individuals experience clinically relevant adverse psychosocial effects after counseling
[2-13].

It has been estimated that approximately one-third of counseless have some level of unmet need for psychosocial services in relation to genetic counseling
[14,15]. This is not entirely surprising, in that genetic counselors focus primarily on gathering and communicating biomedical information, and often have a ‘teaching’ communication style
[16]. This creates a situation where there is less time available to discuss potentially relevant psychosocial issues.

Patient reported outcome (PRO) measures have been used in a range of health care settings as a tool to improve communication between patients and their health care providers about relevant physical and psychosocial health problems
[17-20]. Facilitating such communication has been hypothesized to have a cascade of effects, including improved provider awareness of their patients’ problems, improved patient care and management, including appropriate referrals, and ultimately, improved health outcomes
[21-24].

Recently, we developed a psychosocial screening questionnaire specifically for the clinical cancer genetics setting, the Psychosocial Aspects of Hereditary Cancer (PAHC) questionnaire
[25]. The PAHC questionnaire comprises: (1) 26 items organized into 6 problem domains (i.e., hereditary predisposition, family- and social issues, practical issues, general emotional issues, cancer-specific issues, and, for those who have children, children-specific issues), with response options ranging from 1 (‘not at all’) to 4 (‘very much’); (2) a question, per problem domain, about the desire to talk to a specialized psychosocial health professional; and (3) the Distress Thermometer (DT), a single item visual analogue scale ranging from 0–10, with 0 representing ‘no distress,’ and 10 ‘severe distress’
[26].

The aim of this randomized, controlled trial is to evaluate the efficacy of the PAHC questionnaire when used routinely in daily clinical cancer genetics practice in: (1) facilitating communication during genetic counseling sessions about relevant psychosocial issues; (2) increasing genetic counselors’ awareness of the psychosocial problems of their counselees; and (3) facilitating the appropriate management of these cancer genetic-specific psychosocial problems. Specifically, our primary research hypotheses are that the use of the PAHC questionnaire during genetic counseling will:

(1) increase significantly the number of psychosocial issues discussed during genetic counseling sessions;

(2) increase significantly the genetic counselors’ awareness of the psychosocial problems experienced by their counselees; and

(3) improve significantly the management of cancer genetic-specific psychosocial problems as evidenced by the referrals to psychosocial care and/or to sources of information about psychosocial issues. Additionally, we hypothesize that the routine use of the PAHC questionnaire will:

(4) increase significantly the number of discussed issues initiated by the counselor;

(5) increase significantly counselees’ satisfaction with the counseling process;

(6) decrease significantly counselees’ levels of cancer worry and distress during and after the genetic counseling process;

(7) decrease significantly the cancer genetic-specific problems experienced by the counselee after the genetic counseling process; and

(8) *not* increase significantly the total duration of the genetic counseling session.

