### Secondary outcome measures

Secondary outcomes include: (1) initiation of problem discussion; (2) the time devoted to discussing each psychosocial problem and the total duration of the counseling session; (3) cancer worries and general psychological distress; (4) cancer genetics-specific psychosocial problems; and (5) counselees’ and counselors’ satisfaction with the genetic counseling and with the intervention (the latter for the intervention group only).

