#### Initiation of psychosocial issue discussion, and time devoted to such discussions

The audiotapes of the counseling sessions will be coded for who initiated the discussion of each specific psychosocial issue (i.e., the counselee or the counselor), the amount of time spent talking about psychosocial issues, and the total length of the counseling session.

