### Sample size and power calculations

We have based the sample size estimates on expected differences between the intervention group and the control group in communication between the genetic counselors and counselees about psychosocial issues. Overall power calculations for estimating sample size requirements were based on the following criteria for defining a substantively meaningful statistical association: (1) power of 0.80, (2) alpha of 0.05, and an (3) effect size “d” of 0.4. With these criteria, 99 cases per study arm are needed, resulting in a total sample size of 198 cases.

We anticipate that approximately 25% of the counselees will not have more than one counseling session and thus will not have a DNA-test disclosure session. Therefore, in order to have sufficient power in the second phase of the trial, we will include 264 participants at the start of the trial.

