#### Secondary research hypotheses

We will employ analysis of (co)variance to evaluate group differences in the frequency of with which the genetic counselor initiated the discussion of psychosocial issues. Analysis of (co)variance will also be used to evaluate group differences in the amount of counseling time spent discussing psychosocial issues, and the total length of the counseling session. To evaluate group differences in cancer worries and general distress, we will use analysis of covariance, with the previous scores on these questionnaires as covariate. Logistic regression analysis will be used to evaluate differences between groups in the prevalence of cancer genetics-specific problems. Group differences in satisfaction with the genetic counseling process will be examined with Student’s t-tests and chi square tests, where appropriate. Intervention group and counselor satisfaction with the intervention will be reported descriptively.

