### Methodological issues

A major strength of the study is its use of a randomized design that will ensure high levels of internal validity. The relatively large sample size, the multicenter approach, and the heterogeneity of the study sample will increase the external validity and generalizability of the findings.

Several possible limitations of the study should also be noted. First, due to the nature of the intervention, it is not possible to blind the genetic counselors, nor the counselees, nor the raters of the audiotapes to group allocation. This carries with it the risk of contamination, particularly on the part of the counselors. That is, any given genetic counselor will be seeing both counselees assigned to the intervention group and the control group. Thus, it is conceivable that the counselors’ experience with the intervention (i.e., receiving personalized feedback regarding the counselees’ self-reported psychosocial problems) will also affect the way they interact with counselees in the conrol group. We would note, however, that any such carry over effect will have a conservative effect on the study (i.e., that, if anything, it will make it more difficult to observe significant group differences on the primary study outcomes). A second possible limitation of the study will depend on the observed prevalence of psychosocial problems among counselees. If the prevalence is low, then it will be more difficult to detect group differences in the various study outcomes. Finally, due to funding limits, the follow-up period for the second phase of the trial is relatively short (only 4 months).

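### Secondary hypothesis (8), that sessions do not get longer, is worded so that a non-significant difference test would count as support, which such a test cannot give

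*Protocol article*

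**What the plan says.** All references are to the protocol article.

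- **Background, hypothesis (8).** Last of the additional hypotheses: routine use of the questionnaire will not "increase significantly the total duration of the genetic counseling session". The word for not is italicised in the article, so the absence of a significant increase is itself the prediction.
- **Secondary outcome measures.** Duration is a secondary outcome, listed as "the time devoted to discussing each psychosocial problem and the total duration of the counseling session".
- **Secondary research hypotheses.** Analysis of (co)variance will be used to "evaluate group differences in the amount of counseling time spent discussing psychosocial issues, and the total length of the counseling session". This is the method also named for counselor-initiated discussion, where a difference is hoped for. No margin or confidence-limit criterion is given for duration.
- **Sample size and power calculations.** The trial is sized for another outcome: "We have based the sample size estimates on expected differences between the intervention group and the control group in communication" between counselors and counselees. The result is that "99 cases per study arm are needed, resulting in a total sample size of 198 cases", raised to 264 because about 25% are expected to have no second session.
- **Methodological issues.** Each counselor sees counselees of both arms, and the article says that "any such carry over effect will have a conservative effect on the study". The bracket that follows explains this as greater difficulty in seeing significant differences on the primary outcomes.

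**The concern.** Hypothesis (8) is the null hypothesis of the test named for it. Failing to reject a null is weak evidence for it: the same result arises when there is no increase, when duration varies widely, when few sessions are available, or when the arms have been made alike by carry-over. A hypothesis met by non-significance is therefore easier to meet the less informative the data are.

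A real increase is plausible on the trial's own reasoning. Hypotheses (1) and (4) predict that more issues will be discussed and that more will be raised by the counselor, and the Background notes that time for psychosocial issues is already short. If sessions do lengthen, the plan as worded could still end in a statement that they did not.

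Contamination adds to this. Pulling the arms together makes a superiority hypothesis harder to show, but makes hypothesis (8) easier to show.

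**Working it through.** **1. The plan's own sample size.** Inputs from Sample size and power calculations: d = 0.4, alpha 0.05 (two-sided reproduces the figure; one-sided would give 78 per arm), power 0.80.

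n per arm = 2(1.960 + 0.842)² / 0.4² = 98.1, rounded up to 99; total 198. Allowing for 25% without a second session: 198 / 0.75 = 264, or 132 per arm. The stated figures reproduce and are not in dispute. They give 132 per arm for the first session (phase I) and 99 per arm for the telephone session (phase II).

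**2. Chance that the planned test shows no significant increase when there is one.** Let d be the true increase in units of the SD of session duration (SD not given in the article). With a two-sided 5% t-test, the chance is P(T ≤ t₀.₉₇₅), where T is non-central t with 2n − 2 degrees of freedom and non-centrality d√(n/2).

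- n = 132: √66 = 8.124, critical value 1.969.
- n = 99: √49.5 = 7.036, critical value 1.972.

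| True increase | Non-centrality, 132 / 99 | No significant increase, 132 / 99 |
|---|---|---|
| 0.20 SD | 1.625 / 1.407 | 63% / 71% |
| 0.25 SD | 2.031 / 1.759 | 47% / 58% |
| 0.30 SD | 2.437 / 2.111 | 32% / 44% |
| 0.40 SD | 3.250 / 2.814 | 10% / 20% |

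The 95% confidence interval half-width is t₀.₉₇₅√(2/n) = 0.24 SD / 0.28 SD.

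**3. Effect of contamination.** Suppose carry-over shrinks a true 0.4 SD increase by a fraction c (an assumption; the article gives no figure). Replacing d by 0.4(1 − c) in step 2:

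| c | Observable increase | No significant increase, 132 / 99 |
|---|---|---|
| 0 | 0.40 SD | 10% / 20% |
| 25% | 0.30 SD | 32% / 44% |
| 50% | 0.20 SD | 63% / 71% |

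**4. What a margin would achieve.** With margin m, no true difference and one-sided 0.025, power = Φ(m√(n/2) − 1.960). The margins are assumptions.

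| Margin | Power, 132 / 99 |
|---|---|
| 0.25 SD | 53% / 42% |
| 0.30 SD | 68% / 56% |
| 0.35 SD | 81% / 69% |
| 0.40 SD | 90% / 80% |

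About 80% power therefore needs a margin near 0.35 SD in phase I or 0.4 SD in phase II.

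**5. A margin does not remove the contamination bias.** With m = 0.4 SD and a true increase of 0.4 SD, the chance of wrongly passing is Φ(0.4c√(n/2) − 1.960): 2.5% / 2.5% at c = 0, 13% / 10% at c = 25%, 37% / 29% at c = 50%.

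All figures treat sessions as independent and use an unadjusted comparison of means.

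**The case against.** The strongest reply is that the article nowhere says a p-value above 0.05 will be reported as proof of no increase. It says only that group differences in length will be evaluated and, under Statistical analyses, that effect sizes will be calculated. A margin is the sort of detail an analysis plan may hold, and that plan is not at hand. This stands as far as the missing margin goes. It does not rescue the hypothesis, whose published wording makes absence of significance the thing to be found.

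A second reply is that increases of 0.20 to 0.30 SD are small. At 0.4 SD, the effect size the article treats as meaningful, the test misses only 10% / 20%. That is correct and is why the 0.4 SD row is shown. But 0.4 was chosen for communication, not for duration, and nothing in the article says that a smaller lengthening would be unimportant.

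A reader might also infer three stronger points that the text does not support:

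- *That the article claims contamination is conservative for every outcome.* The opening words are broad, but the bracket limits the argument to the primary outcomes, and duration is secondary. The article is silent on hypothesis (8), not wrong about it.
- *That the Conclusion rests on a claim of no extra time.* It speaks of rising demand for counseling and pressure on counselors, and does not mention session length.
- *That the interval half-width of 0.24 SD makes a tight margin workable.* Half-width is not power: a 0.25 SD margin has only 53% / 42%.

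**Conclusion.** The point holds for the wording of hypothesis (8) combined with the difference test named for it. A non-significant result would be read as support, and it would occur in 63% / 71% of trials at a true 0.20 SD increase, falling to 10% / 20% at 0.40 SD (132 / 99 per arm). Dilution between arms raises these chances, so the reassurance given on contamination for the primary outcomes should not be carried over to duration.

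The probabilities depend on the planned arm sizes, two-sided testing at 0.05 and independent sessions. The SD of duration, the degree of dilution and any margin are not in the article, so the results are in SD units over a range.

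Severity is minor to moderate. The hypothesis is secondary, and no primary outcome, sample size or allocation depends on it.

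**What to change.** Before the data are analysed:

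1. Restate hypothesis (8) as: the mean increase in session duration is smaller than a stated number of minutes, agreed with the clinics as the largest acceptable, with a separate figure for the first session and the telephone session if they differ.
2. Claim no relevant increase only if the upper limit of the 95% confidence interval for the difference (intervention minus control) lies below that figure. Otherwise report the estimate and interval and make no claim that duration did not increase. If no margin can be agreed, this second form of reporting is enough by itself.
3. Add one sentence to Methodological issues: the conservative-contamination argument concerns the primary outcomes; for hypothesis (8) dilution favors the hypothesis, and a margin does not remove that bias.

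The cost is a few sentences and agreement on a margin; no new data are needed. The downside is that, with no true difference, a margin tighter than about 0.35 SD in phase I or 0.4 SD in phase II leaves power below 80%, so the result may be inconclusive.

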## Methods/design

This is a prospective, multicenter, randomized controlled trial in which participants will be randomly allocated to: (1) an intervention group that completes the PAHC questionnaire prior to genetic counseling, the results of which are provided to the genetic counselor; or (2) a control group that completes the PAHC questionnaire, without feedback being given to the genetic counselor. The study consists of two phases. In the first part of the study, the focus is on the efficacy of the intervention during the first face-to-face genetic counseling session. The second phase of the study is concerned with the efficacy of the intervention during a telephone follow-up held approximately 4 weeks after DNA-test results are disclosed in a final face-to-face counseling session.

The primary outcome measures are counselor-counselee communication about psychosocial problems, counselors’ awareness of their counselees’ psychosocial problems, and improved management of those problems. Secondary outcomes include satisfaction with the counseling process, cancer worries, psychological distress, and prevalence of psychosocial problems. The design of the study and the anticipated flow of participants are displayed graphically in Figure 
1.

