### Recruitment and randomization

All eligible counselees will receive an invitation letter from the family cancer clinic, an informed consent form, a baseline questionnaire, and a return envelope three weeks before their first counseling session. Upon returning the completed informed consent form and the baseline questionnaire, we will randomize the participants on a 1:1 basis to either the intervention group or the control group. The minimization method will be used to balance the intervention and control group for each counselor in terms of gender and the cancer syndrome for which genetic counseling is requested
[28]. Neither the counselees nor the counselors will be (or can be) blinded to group assigment.

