### Intervention group procedure

Within the Netherlands, individuals seeking cancer genetic counseling routinely undergo a first consultation with a genetic counselor or a clinical geneticist and, when opting for a DNA-test, a final counseling session during which the DNA-test results are disclosed to the counselee. If indicated, screening recommendations for the patient and relatives are discussed within these sessions. The study intervention will take place within this standardized process, at the time of the first face-to-face genetic counseling session (phase I), and by telephone 4 weeks after the final face-to-face counseling session (phase II). The participants in the intervention group will be asked to complete the PAHC questionnaire either via the internet or, if preferred, by mail shortly before the face-to-face and the telephone follow-up counseling sessions. The counselee’s responses to the PAHC questionnaire will be made available to the genetic counselor prior to the counseling sessions.

The PAHC questionnaire consists of 26 questions addressing psychosocial problems and worries that are specifically relevant to counselees within the cancer genetics counseling and testing setting. The content of the PAHC questionnaire is organized into the following six domains: (1) hereditary predisposition; (2) family- and social issues; (3) practical issues; (4) general emotional issues; (5) cancer-specific issues; and, for those who have children 6) children-specific issues. The number of items per domain varies between 2 and 7. All 26 items are scored on a 4-point, Likert-type scale ranging from 1 (“not at all”) to 4 (“very much”). The PAHC questionnaire is supplemented by the Distress Thermometer (DT), a visual analogue scale ranging from 0–10 (no distress-severe distress). The timeframe of the PAHC questionnaire and the DT is the previous week. Per problem domain assessed by the PAHC questionnaire, the respondent is asked to indicate whether (s)he would like to receive professional psychosocial support
[25].

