### Control group procedure

Counselees in the control group will complete the PAHC questionnaire and DT as described above for the intervention group. However, the results of these questionnaires will not be provided to the genetic counselors.

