#### Management of psychosocial problems

The audiotapes of the counseling sessions will also be used to evaluate how the counselees’ psychosocial problems are managed. Specifically, the study-specific checklist will be used to code whether counselees were referred to additional sources of information about how to deal with psychosocial problems (e.g., websites or written materials) or to additional psychosocial counseling. The counselees will be asked to report their actual use of psychosocial services.

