#### Main research hypotheses

We will evaluate group differences in the number of psychosocial issues discussed during the genetic counseling sessions using analysis of (co)variance. We will assess counselors’ awareness of their counselees’ psychosocial problems by calculating the agreement between counselees’ and counselors’ on their ratings, per domain, of the psychosocial problems experienced by the counselees. We will calculate an Intraclass Correlation Coefficient (ICC2.1.A
[34]) per domain for both the intervention and control group. Group differences will be assessed by treating the ICC’s as Pearson correlation coefficients and using Fisher’s r-to-z transformation to test for statistical differences per domain. Analysis of (co)variance will also be used to evaluate group differences in referral to additional information sources and/or referral to psychosocial care services, and the actual use of such services.

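### Phase II is described as testing the intervention during the telephone call, but one randomization with feedback at both sessions or neither supports only a test of the two-session strategy

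*Protocol article*

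**What the plan says.** The protocol article sets two parallel targets under Methods/design. In phase I "the focus is on the efficacy of the intervention during the first face-to-face genetic counseling session". For phase II it says: "The second phase of the study is concerned with the efficacy of the intervention during a telephone follow-up".

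Allocation happens once. Under Recruitment and randomization: "Upon returning the completed informed consent form and the baseline questionnaire, we will randomize the participants on a 1:1 basis". No second randomization and no telephone-only feedback arm is described. The Intervention group procedure places the intervention at both the first session and the call, with the printed results attached to the medical record. Control counselees complete the same questionnaires, but "the results of these questionnaires will not be provided to the genetic counselors".

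The quantities counted at the call are those phase I is meant to change. The first primary hypothesis (Background) is that the questionnaire will "increase significantly the number of psychosocial issues discussed during genetic counseling sessions". Management is assessed by using the audiotapes to "code whether counselees were referred to additional sources of information about how to deal with psychosocial problems" or to psychosocial counseling, and the analysis compares "group differences in referral to additional information sources and/or referral to psychosocial care services, and the actual use of such services".

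Phase II also drives the sample size: under Sample size and power calculations, enrolment rises from 198 to 264 so that phase II is adequately powered.

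**The concern.** If phase I works as hypothesized, the arms reach the call in different states. Intervention counselees will already have discussed more issues and been referred more often. The counselor may already know their problems, and the first printout is in the record. A difference at the call then reflects feedback given at the call together with whatever phase I left behind.

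The carry-over need not act in one direction. Earlier referral may leave fewer people to refer at the call. Earlier feedback may raise the counselor's awareness at the call, or make both parties readier to talk about psychosocial issues. The carry-over discussed under Methodological issues is different: it concerns counselors applying their experience with the intervention to control counselees. Its argument that the effect is conservative does not extend to carry-over within a counselee.

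What is at stake is interpretation. Under the present wording, a null or reversed call-only referral result could be reported as telephone feedback failing, and a positive one as telephone feedback working. The design supports neither statement.

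**Working it through.** **1. What the arms contrast**

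| Arm | First session | Telephone call |
|---|---|---|
| Intervention | feedback | feedback |
| Control | none | none |

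Let T be the effect of telephone feedback on a call outcome, and C everything phase I feedback contributes to that outcome, including any interaction. The difference by arm estimates T + C. Separating T would need counselees without phase I feedback who receive it at the call, or a new randomization before the call. Neither is described.

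**2. The plan's own figure**

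Inputs (Sample size and power calculations): d = 0.4, power 0.80, alpha 0.05, 25% without a disclosure session.

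n per arm = 2(1.960 + 0.842)² / 0.4² = 98.1, rounded up to 99; total 198; 198 / (1 − 0.25) = 264. This matches the plan. Sidedness is not stated; two-sided reproduces 99, whereas one-sided gives 78. The arithmetic is not at fault.

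**3. How sensitive phase II is to carry-over**

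The size is not in the documents, so a range is assumed. With a true call effect of 0.4 SD and c SD subtracted by carry-over (negative c means it adds), power at 99 per arm is about Φ[(0.4 − c)/√(2/99) − 1.96].

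| c (SD, assumed) | Expected difference | Power in favor of intervention |
|---|---|---|
| −0.2 | 0.6 | 99% |
| −0.1 | 0.5 | 94% |
| 0 | 0.4 | 80% |
| 0.1 | 0.3 | 56% |
| 0.2 | 0.2 | 29% |

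At c = 0.4 the expected difference is zero; above that it reverses.

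**4. Referral illustration**

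Assumptions: 25% of counselees need referral; those in need and not yet referred are referred with probability p1 at the first session and p2 at the call; nobody is referred twice; no new need arises. Control: p1 = p2 = 0.30. Intervention: p1 = p2 = 0.60. The 25% borrows the Background figure for clinically relevant adverse effects after counseling, which is not a referral-need rate. Need multiplies both arms equally, so its value does not alter the direction.

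| Quantity | Formula | Intervention | Control |
|---|---|---|---|
| First session | 0.25 × p1 | 0.25 × 0.6 = 15.0% | 0.25 × 0.3 = 7.5% |
| Call only | 0.25 × (1 − p1) × p2 | 0.25 × 0.4 × 0.6 = 6.0% | 0.25 × 0.7 × 0.3 = 5.3% |
| Either session | sum | 21.0% | 12.8% |

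If p1 in the intervention arm is 0.70, the call shows 0.25 × 0.3 × 0.6 = 4.5% vs 5.3%, a reversal, while the cumulative figures are 22.0% vs 12.8%. Reversal requires 0.25 × (1 − p1) × 0.6 < 0.0525, that is p1 > 0.65.

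**5. Relaxing the no-new-need assumption**

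Suppose a fraction g of counselees acquires new need by the call, referred at 0.60 and 0.30. In the reversal case the call figures become 0.045 + 0.6g vs 0.0525 + 0.3g, which are equal at g = 0.0075 / 0.3 = 2.5%. With g = 10% they are 10.5% vs 8.25%, and in the base case 12.0% vs 8.25%.

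**6. What a cumulative endpoint would show**

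In the base case the cumulative difference is 21.0 − 12.75 = 8.25 points, of which 15.0 − 7.5 = 7.5 points arise at the first session.

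**The case against.** The strongest reply is that the protocol never claims an effect of telephone feedback on its own. The intervention is defined as taking place at both sessions, and the stated aim is efficacy in routine use. On that reading Methods/design merely names the session at which the two-session intervention is assessed, and the comparison by arm is randomized and sound. This stands as regards validity. It does not clear the wording, which gives the call a session-specific target parallel to that of phase I and nowhere says that the contrast is feedback at both sessions versus neither.

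Second, a call-only referral endpoint is partly inferred. The management section refers to sessions in the plural, and service use during the study (Sociodemographic and clinical data) is already cumulative. Whether referrals are scored per session or pooled may be left to a fuller document. This is fair, and is why the point rests on the stated target rather than on a missing scoring rule.

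Third, the depletion model is fragile. The PAHC is repeated before the call with a previous-week timeframe, after DNA disclosure, and referral to websites or written materials can recur. Modest new need removes the reversal, and the base case favors the intervention even without it. This also stands.

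Fourth, a cumulative endpoint has its own weakness: it would mostly repeat phase I and could be positive if the call added nothing. It therefore should not replace the call-only counts.

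**Conclusion.** The stated phase II target and the design do not match. By arm, phase II validly compares feedback at both sessions with feedback at neither; it does not identify what feedback during the call contributes. That follows from the allocation and the procedures alone and needs no assumed rates.

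The numerical consequence is not known. The 6.0% vs 5.3% at the call, against 21.0% vs 12.8% over both sessions, and the power losses of step 3 show what could happen under assumed rates and assumed carry-over. They are not predictions for this trial.

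A reader might infer that phase II is invalid, or that success in phase I will produce a null or negative phase II. The documents support neither. Randomization protects the two-session comparison, which fits the routine-use aim, and carry-over could equally enlarge the difference. Phase I is unaffected. This is an inexpensive correction that changes what may be concluded, not a flaw that undermines the trial.

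**What to change.** In Methods/design, state that phase II evaluates feedback at both sessions versus feedback at neither and supports no claim about telephone feedback alone.

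Keep the call-only counts and interpret them as effects of the two-session strategy. Beside them, report by arm:
- the proportion ever referred across the first session and the telephone call;
- the number of distinct PAHC issues discussed across those two audiotaped sessions;
- the psychosocial service use during the study that is already collected.

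State the denominator for the two-session summaries, since about 25% of counselees are expected to have no disclosure session. Say also that they cover the first session and the call only: Table 1 does not separately list a recording of the disclosure session.

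Add an interpretive rule. A null or reversed call-only referral result is not to be read as failure of telephone feedback, and a positive cumulative result is not proof that the call added benefit.

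The cost is a few sentences, a little more analysis of recordings that are already to be coded, and no stand-alone efficacy claim for the telephone session.
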